### Sample size

2.4

Sample size calculations are based on the primary outcome (the clinical effective rate at 2 weeks). According to the previous literature,^[34]^ we assumed the clinical effective rate of 73% in the control group and 93% in the experimental group over 14 days. Thus, a sample size of 82 patients is needed to achieve a statistical power of 80% (single-sided type-1 error of 5% in both scenarios). Assuming that 10% of patients are likely to be lost during follow-up, a total of 92 patients will be enrolled.

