### Randomization and allocation concealment

2.5

A member of Sichuan evidence-based Medicine Center of TCM, who does not participate in subsequent trials, uses SAS 9.2 software (SAS Institute Inc., Cary, NC) to generate 92 random serial numbers. Randomization is performed after screening and baseline evaluation, and eligible T2DM-CAP subjects will be randomized in a 1:1 fashion to receive 1 of 2 treatments. The group numbers are provided in continuously numbered, sealed envelopes made of carbonless paper. The envelopes will be held by a research administrator who will not be directly involved in the recruitment or follow-up of any participants. The administrator provides the subjects with their group number on the day of inclusion. Consequently, the subjects, clinical researchers, data managers, outcome assessors, and statisticians do not know the allocations, which not be revealed until the study is completed.

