#### Secondary outcomes

3.3.2

1)**TCM symptom score scale (**at days 4, 8, and 14).2)**Pneumonia severity index** (at days 4, 8, and 14).3)**usage time of antibiotic** (at days 6, 10, and 14).4)**time required for blood sugar to reach the required level (**at days 2, 4, 6, 8, 10, 12, 14).5)**frequency of hypoglycemia (**at days 2, 4, 6, 8, 10, 12, 14).6)**laboratory examination:** including white blood cell count, percentage of neutrophils, C-reactive protein and procalcitonin **(**at days 4, 8, 14).7)**chest CT (**at days 14).8)** Exploratory outcome:** Differences in blood metabolomics between the 2 groups after treatment **(**at days 14).

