### Statistical analysis

3.8

Statistical analysis will be performed at the Sichuan evidence-based Medicine Center of TCM using Statistical Package for the Social Sciences version 22.0 (SPSS 22.0, Chicago, IL). Intention-to-treat and per protocol sets are applied to analyse the efficacy of modified BXXXD. A safety analysis set is used to assess the safety of the study. Missing values are estimated using the principle of the last observation carried forward, with the data from the last study follow-up used as the final results.

Categorical data are tabulated with frequencies or percentages, and continuous data are reported as median or mean ± standard deviation. For the sociodemographic data and baseline variables are conducted using analysis of variance and Chi-squared test. To compare the variables of the same group before and after treatment, a paired *t*test is used. Repeated measures analysis of variance is used to compare the differences among the 2 groups. All statistical tests are bilateral tests and *P* values < .05 is regarded as statistical significance.

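### Repeated secondary outcomes: within-arm paired t-tests cannot show an effect of the granules, and the between-arm ANOVA names no baseline covariate

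*Protocol article*

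**What the plan says.** The protocol article, section 3.8 (Statistical analysis), names three procedures that bear on this point:

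- Within each arm, a paired t-test is used "To compare the variables of the same group before and after treatment".
- Between the arms, "Repeated measures analysis of variance is used to compare the differences among the 2 groups". No covariate is mentioned. The section does not say whether baseline is one of the time levels, or whether the group effect or the group-by-time term is the treatment test.
- At baseline, "For the sociodemographic data and baseline variables are conducted using analysis of variance and Chi-squared test".

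The same section states that "All statistical tests are bilateral tests", with a threshold of .05, and fills missing values by last observation carried forward.

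Section 3.3.2 schedules the "TCM symptom score scale" and the pneumonia severity index "at days 4, 8, and 14", and the laboratory values on the same three days. Section 2.5 says "Randomization is performed after screening and baseline evaluation". A before-after paired test also presupposes a pre-treatment value for each variable it is applied to.

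Section 3.8 speaks only of variables and does not tie these tests to named outcomes. Applying them to the repeated secondary outcomes is a reading, but the natural one.

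**The concern.** A test of change within one arm does not use the randomised comparison. Section 3.1 gives both arms insulin and antibiotics, and section 2.4 assumes that 73% of control patients will respond. Improvement in each arm is therefore expected whether or not the granules work. A small P value in the experimental arm does not separate the granules from basic treatment, and a pattern of one arm significant and the other not can easily arise by chance.

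The between-arm ANOVA does use the randomised comparison. As described, though, it takes no account of where each patient started. With about 41 evaluable patients per arm, chance differences at baseline carry through to the follow-up values. A baseline covariate would remove much of that noise. Significance tests of baseline variables do not: they test a hypothesis that randomisation makes true, and they leave the treatment estimate unchanged.

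What is at stake is the precision and the reading of the secondary results. Section 4 relies on the TCM score and the pneumonia severity index to support the reliability of the findings.

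**Working it through.** **Plan's own figure.** The article gives no sample-size or power figure for the repeated outcomes. Its only calculation is for the binary primary outcome (section 2.4) and serves here only as the source of the arm size. With unpooled variance and one-sided 5%: (1.645 + 0.842)² × (0.73 × 0.27 + 0.93 × 0.07) / 0.20² = 40.5, so 41 per arm and 82 in total; 82 / 0.9 = 91.1, raised to 92 for equal arms. The stated 82 and 92 reproduce.

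**Inputs below.** From the article: 41 evaluable per arm, three post-baseline visits, two-sided 5%. Assumed, because the article gives none of them: equal variances, a common correlation r between any two visits (baseline included), and the effect sizes. All sizes are in SD units.

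**1. Within-arm paired t-tests when the granules do nothing.** Both arms truly improve by d, with r = 0.5. The SD of a change is √(2 − 2r) = 1, so the noncentrality is d × √41 = 6.40d on 40 degrees of freedom. Let p be the chance that one arm is significant. The arms are independent, so the chance that exactly one is significant is 2p(1 − p), and in half of those cases it is the experimental arm alone.

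| True improvement in both arms | p | Exactly one arm significant | Experimental arm alone |
|---|---|---|---|
| 0.2 SD | 0.240 | 36% | 18% |
| 0.3 SD | 0.466 | 50% | 25% |
| 0.4 SD | 0.705 | 42% | 21% |
| 0.5 SD | 0.878 | 22% | 11% |
| 0.8 SD | 0.999 | 0.2% | 0.1% |

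At 0.8 SD the discordance disappears because both arms are nearly always significant, which says nothing about the granules either.

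**2. Between-arm comparison, like for like.** The target is the average over days 4, 8 and 14. The variance factors are:

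- unadjusted: (1 + 2r)/3
- baseline-adjusted: (1 + 2r)/3 − r²

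Power is for a constant 0.5 SD effect at 41 per arm. For example, at r = 0.5 unadjusted, SE = √(2/41 × 0.667) = 0.180, 0.5/0.180 = 2.77, and Φ(2.77 − 1.96) = 79%.

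| r | Unadjusted | Adjusted | Variance reduction | Power, unadjusted | Power, adjusted |
|---|---|---|---|---|---|
| 0.3 | 0.533 | 0.443 | 17% | 87% | 93% |
| 0.5 | 0.667 | 0.417 | 38% | 79% | 94% |
| 0.7 | 0.800 | 0.310 | 61% | 72% | 98% |

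At r = 0.2 the reduction is only 9%. If baseline is instead a time level and the 3-degree-of-freedom group-by-time term is the test, power at r = 0.3, 0.5 and 0.7 is 47%, 63% and 86%. That term uses baseline, but less efficiently than a covariate.

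**3. Why the target must be held fixed.** Take a 0.6 SD effect, r = 0.5 and 46 per arm (all enrolled).

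- Effect complete from day 4, unadjusted average of days 4, 8 and 14: SE = √(2/46 × 0.667) = 0.170; 0.6/0.170 = 3.52; power 94%.
- Same effect, baseline-adjusted day 14 alone: variance factor 1 − r² = 0.75; SE = 0.181; 0.6/0.181 = 3.32; power 91%.
- Same effect, baseline-adjusted average: SE = √(2/46 × 0.417) = 0.135; 0.6/0.135 = 4.46; power 99%.
- Effect building linearly to 0.6 SD, baseline counted as a fourth level, group effect tested: the mean effect is 0.3 and the variance factor (1 + 3r)/4 = 0.625; power 44%.

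The last figure set against 91% mixes a change of target, an assumed time course and an assumed coding of baseline with the effect of adjustment. The table in step 2 isolates adjustment.

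**The case against.** The strongest reply is that this is a short statistical section in a journal article and that the full analysis plan is not shown. Which ANOVA term is tested, and whether baseline is a level or a covariate, are details that an article commonly leaves to that plan. A randomised between-arm comparison is specified, nothing says that efficacy will be claimed from within-arm results, and only secondary outcomes are involved.

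Much of this stands, and it limits what may be inferred:

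- A reader might infer that the plan rules out baseline adjustment. It does not; it is silent.
- A reader might infer that the sponsor intends to present within-arm P values as evidence of efficacy. No text says so. The risk is one of later reporting.
- A reader might infer that baseline is used only to compare the arms at entry. The paired test uses it as well, and the group-by-time term would too if baseline is a level.
- A reader might infer a loss of about half the power (44% against 91%). That needs baseline as a time level, the group effect as the test, a linear build-up and two different targets. With days 4, 8 and 14 only and a full effect from day 4, the planned test has 94% power and overtakes the day-14 adjusted contrast at 91%.

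What does not fall away is the choice of named methods. The paired t-tests and the baseline tests are prescribed outright and are subject to the same .05 threshold as every other test, with nothing marking them as descriptive. The between-arm method is named without a covariate, although a better use of the same data is available.

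**Conclusion.** The point holds as an improvement of minor to moderate weight, confined to the repeated secondary outcomes; the binary primary outcome at day 14 is untouched.

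The argument against the within-arm tests rests on the design itself, since both arms are actively treated. Its illustrated size (22% to 50% discordance with no treatment effect) assumes r = 0.5, 41 per arm and a common improvement between 0.2 and 0.5 SD.

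The argument for adjustment is firm in direction: under the common-correlation model, the baseline-adjusted comparison is never less precise than the unadjusted comparison of the same average. Its size cannot be known from the article. The 17% to 61% variance reduction is a range over assumed correlations of 0.3 to 0.7, not an estimate for this trial.

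**What to change.** In section 3.8:

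1. Name a baseline-adjusted between-arm comparison, reported with a 95% CI, as the inferential analysis of the TCM score, pneumonia severity index and laboratory values. Either ANCOVA serves, or a mixed model on days 4, 8 and 14 with treatment, visit, treatment-by-visit and the baseline value.
2. State before unblinding whether the treatment estimate is the day-14 difference or the average over the three visits, since step 3 of the working shows that this choice matters.
3. If the mixed model is chosen, fit it to observed data and not to last-observation-carried-forward values, and amend the missing-data sentence to match.
4. Report within-arm change and baseline characteristics descriptively, without significance tests.

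The cost is wording. No extra patients or visits are needed, and the paired test already presupposes the baseline values. The sponsor should confirm that each of these outcomes is recorded at the baseline evaluation, because section 3.3.2 lists only days 4, 8 and 14 and the schedule figure could not be read here.

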#### Primary outcome

3.3.1

Disease outcomes include cure, significant effect, effective, and ineffective. The main result is the total clinical effectiveness after treatment (day 14) of the 2 groups, that is, the sum of cure rate, apparent efficiency and effective.

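### The only between-group outcome method named in section 3.8, repeated measures ANOVA, does not fit a binary primary outcome assessed once at day 14 or the two-proportion basis of the sample size

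*Protocol article*

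**What the plan says.** Section 3.3.1 (Primary outcome) grades each patient in four categories: "Disease outcomes include cure, significant effect, effective, and ineffective". It then collapses the first three into one responder rate, "that is, the sum of cure rate, apparent efficiency and effective", and fixes the time: "The main result is the total clinical effectiveness after treatment (day 14) of the 2 groups".

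Section 2.4 (Sample size) rests on the same rate at 2 weeks: "we assumed the clinical effective rate of 73% in the control group and 93% in the experimental group". It asks for 80% power at a one-sided 5% level, which gives 82 patients, or 92 after 10% loss.

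Section 3.8 (Statistical analysis) names its methods by purpose:

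- Baseline comparison: "For the sociodemographic data and baseline variables are conducted using analysis of variance and Chi-squared test".
- Change within a group: "To compare the variables of the same group before and after treatment, a paired *t*test is used".
- Comparison between groups: "Repeated measures analysis of variance is used to compare the differences among the 2 groups".

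Categorical data are otherwise mentioned only as being tabulated with frequencies or percentages. All tests are two-sided at 0.05.

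**The concern.** Repeated measures ANOVA models a continuous response observed at two or more times in the same patient. The primary outcome is a binary status at a single time, so there is no within-patient time factor to model and no continuous response. The paired t test does not help: it works within one group, and a response category has no pre-treatment value to pair with. The chi-squared test would serve, but the text ties it to baseline variables.

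At stake is the link between the design and the confirmatory analysis. The trial is sized to compare two proportions, and the analysis section does not name such a comparison for the outcome that decides success. An analysis plan that follows section 3.8 literally cannot analyse the primary outcome properly. One that analyses it properly has to narrow or depart from section 3.8.

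**Working it through.** **1. Does the sample size rest on a two-proportion comparison?**

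Inputs from section 2.4: control rate 0.73, experimental rate 0.93, one-sided alpha 0.05 (z = 1.645), power 0.80 (z = 0.842), 10% loss. Allocation is 1:1 (section 2.1).

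Unpooled formula: n per arm = (1.645 + 0.842)² × (0.73 × 0.27 + 0.93 × 0.07) / (0.93 − 0.73)²

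- (1.645 + 0.842)² = 6.185
- 0.73 × 0.27 + 0.93 × 0.07 = 0.1971 + 0.0651 = 0.2622
- 6.185 × 0.2622 / 0.04 = 40.5, rounded up to 41 per arm, 82 in total
- 82 / 0.90 = 91.1, rounded up to 92

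Both published figures reproduce. Other one-sided versions do not give 82: the pooled formula gives 43 per arm (86), the pooled formula with continuity correction 53 per arm (106), and the arcsine formula 40 per arm (80). The published number therefore matches an uncorrected, one-sided comparison of two independent proportions.

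**2. Which method in section 3.8 can take the primary outcome?**

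| Method named | Purpose stated | Fits a yes/no status at day 14? |
|---|---|---|
| ANOVA | Sociodemographic and baseline variables | No: wrong purpose, and meant for continuous data |
| Chi-squared | Sociodemographic and baseline variables | Yes by data type, but not assigned to it |
| Paired t test | Before versus after, same group | No: within group, continuous |
| Repeated measures ANOVA | Differences between the 2 groups | No: one time point, not continuous |

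The one method assigned to between-group comparison does not suit the primary outcome. The one method that would suit it is assigned elsewhere.

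**3. Where does repeated measures ANOVA fit?**

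Section 3.3.2 lists the TCM symptom score, the pneumonia severity index and the laboratory values at days 4, 8 and 14. These are repeated, numerical measures, and the method can be applied to them.

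**4. Context: does it matter which two-proportion test is named?**

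Exact power by enumerating both binomial distributions, at 73% versus 93% and the two-sided 5% level of section 3.8:

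| Per arm | Pearson | Fisher exact | Continuity-corrected |
|---|---|---|---|
| 46 (all 92 enrolled) | 76.7% | 65.8% | 64.2% |
| 41 (82 evaluable) | 71.4% | 61.2% | 56.4% |

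The gap between Pearson and the other two is 10.9 and 12.5 points at 46 per arm, and 10.2 and 15.0 points at 41 per arm. One possible result near the planned effect is 34/46 (74%) versus 42/46 (91%): p = 0.028 by Pearson, 0.052 by Fisher and 0.054 with continuity correction.

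**The case against.** The strongest defence is that the sentence was never meant for the primary outcome. It follows the sentence on before-and-after change, so it can be read as the between-group counterpart for serially measured variables, and section 3.3.2 has several. On that reading no test is misassigned; the primary test is merely left out. A condensed article may leave the exact test to an analysis plan that is not shown. The baseline sentence is also grammatically broken, so its limit on the chi-squared test may not be deliberate, and the sample size makes the intended comparison evident.

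Much of this is fair. The intention is probably as described, and silence about a test variant or interval method would not be a finding. What remains is that section 3.8 is not silent: it states a between-group method without restriction, and nothing in the text confines that method to the repeated secondary outcomes. If that restriction is what is meant, writing it down is half of the correction.

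Three stronger inferences are tempting, and the documents do not support them:

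- A reader might infer that the confirmatory test will be picked once the results are known. Nothing shows this. A separate plan could fix the test beforehand, and sections 2.5 and 2.6 keep the statisticians blinded.
- A reader might infer that the sample size presupposes a two-sided Pearson test. Section 2.4 names no test and uses a one-sided level, and 82 comes from the unpooled formula. The pooled variance that corresponds to Pearson gives 86.
- A reader might take the power differences as the cost of naming repeated measures ANOVA. They compare three valid 2x2 tests with one another. Their shortfall from 80% also includes the effect of moving from a one-sided to a two-sided level, which is a separate matter.

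**Conclusion.** The point holds as a mismatch in what is stated. The between-group method in section 3.8 fits neither the binary day-14 primary endpoint in section 3.3.1 nor the two-proportion calculation in section 2.4. This follows from the wording and the type of outcome, and it rests on no numerical assumption.

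It does not show that the trial will be analysed wrongly, and it does not disturb the published 82 and 92, which reproduce under their own assumptions. The error has no power figure of its own. The 10 to 15 point spread between 2x2 tests assumes true rates of 73% and 93%, equal arms and a two-sided 5% level. It serves only to show why the correction should name one test and not just a class of tests.

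**What to change.** In section 3.8:

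1. State that the day-14 total effective rate is compared between groups in the intention-to-treat set by one prespecified two-proportion test, for example the uncorrected chi-squared test, and reported as a risk difference with its 95% CI.
2. Restrict repeated measures ANOVA to continuous outcomes measured repeatedly, for example the TCM symptom score, the pneumonia severity index and the laboratory values.

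If an analysis plan exists, it should carry the same wording. The cost is about two sentences, with no change to data collection, visits or the number enrolled.

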## Discussion

4

In China, T2DM shows the “4 high” characteristics of high morbidity, high disability, high mortality and high disease burden. What more, with the increase in the prevalence of T2DM, the prevalence of CAP has also increased significantly.^[8–9]^ Although insulin and antibiotics have a good effect on the treatment of the disease in theory, these measures still cannot completely control the progress of the disease in practice, mainly due to insulin resistance and/or antibiotic resistance. CHM has been widely used in the treatment of diabetes or pulmonary infection in China for a long time due to its low probability of adverse reactions. Our research group has been engaged in TCM treatment of diabetes and related complications nearly 20 years. BXXXD has been proved to be effective in clinic and experimental studies.^[28–30]^ Modified BXXXD is suitable for pulmonary infection in patients with diabetes according to the theory of TCM. It has the effects of regulating lung qi, resolving phlegm, relieving cough and relieving asthma. However, the efficacy and safety of modified BXXXD in the treatment of T2DM with CAP have not been universally recognized. Thus, a prospective trial is needed to conclusively determine the effectiveness and safety of modified BXXXD for T2DM-CAP.

To the best of our knowledge, this is the first clinical study to investigate the efficacy of modified BXXXD combined with western medicine in the treatment of T2DM-CAP. In our study, we will employ validated objective tools such as TCM symptom score scale and pneumonia severity index. These measurements improve the reliability and generality of the results. In addition, this trial will also probe into the pathogenesis of T2DM-CAP and the action mechanism of TMC from the perspective of metabonomics. Although the study has limitations such as small sample size, short treatment period, and single-center design. The results of the trial will provide a preliminary objective evidence for the efficacy of modified BXXXD of T2DM-CAP. In the future, a multicenter randomized controlled trial with a large sample and the implementation of multidimensional comprehensive evaluations should be performed.
